### 2.9. Variables

The study variables will mainly be extracted from the following sources: BDLPA; the Andalusian Population Health Database (BPS, Base Poblacional de Salud) [71]; the Andalusian Environmental Information Network (REDIAM) [72]; the Andalusian Epidemiological Surveillance System (SVEA) [73] and the ESSOCgeneral, ESSOCzones, and ESSOC + 55 surveys.

The personal data of the participants selected for the interview (name, surname, and telephone number) are extracted from the BDLPA. In addition, the BDLPA is linked annually with a repository of georeferenced buildings so that the postal address and coordinates (250 m × 250 m grid) in the territory can be extracted. This will allow us to extract geographical factors (urbanisation degree and population density, among others) via other IECA registries, and environmental factors (pollution and temperature, among others) via the REDIAM registry from the Andalusian Regional Government’s Department of Agriculture, Livestock, Fisheries, and Sustainable Development (Consejería de Agricultura, Ganadería, Pesca y Desarrollo Sostenible de la Junta de Andalucía).

From the SVEA registry, epidemiological information related to COVID-19, such as the date and result of the diagnostic test for active infection (PDIA), will be extracted to detect the presence of an active SARSCoV-2 infection, which includes both reverse transcription–polymerase chain reaction (real time RT–PCR) as the antigen (Ag) rapid test; date of the onset of symptoms; close contact of confirmed case with PDIA; local or imported case; occupation as a health or social health professional; need for hospitalisation or admission to an intensive care unit; date of admission, and discharge.

In addition, the clinical information related to chronic diseases [74], functional and cognitive assessments, health resources (volume and cost), population stratification, and drugs consumed, which is obtained from the BPS, will also be added to the valid samples (Table 4). Further information about the variables and the main features of the abovementioned registers can be found in Supplementary Material 3.

With regard to the surveys, each measurement is associated with a questionnaire that coincides, to a significant extent, with previous measurements to enable an analysis of its evolution, and to incorporate new information to analyse specific characteristics present at each moment of the pandemic. Repeating unchanging information in subsequent measurements is avoided in the case of longitudinal samples. The questionnaire used for each measurement is organised into blocks of information, as shown in Table 5.

### 2.10. Data Analysis

The analyses take advantage of all the information available from the measurements and the auxiliary information sources and will be carried out with the free software environment R [81], considering the sample design, as well as the calibration and inference methods described in the previous sections. The use of free software will guarantee transparency and facilitate the replicability of the study.

A table will be prepared for each variable of each measurement, together with the variable’s original response categories, including the valid sample size (*n*), the percentage of lost samples, the population size estimate (N), the relevant statistic (mean or percentage), the 95% CI, and the coefficient of variation (CV), for both the total and the cross-disaggregation per sex and age (16–29/30–44/45–64/65+), as well as per province and urbanisation degree. The sample size is recorded for the total and the categories of the segmentation variable. In the case of cells with CV estimates >20%, the CV will be indicated in a footnote to the table.

The variables shared by all measurements are dichotomized based on the results reported in the previous tables identifying, in each case, the most convenient category to be highlighted based on the previous tables. In addition, a table describing the specific estimates with their corresponding CV will also be created.

Alternatively, to evaluate the changes in each measurement with respect to the first one, both the population affected by the change and the percentage segmented per demographic and territorial variables will be estimated. The *p* value will be calculated to evaluate the effect of such change and will be indicated in a footnote to the table using three categories: *p* < 0.001, *p* < 0.05, and *p* < 0.1.

In the case of variables that coincide in each pair of consecutive measurements (M2–M1, M3–M2, and M4–M3), the estimated percentage of the difference between one measurement and the previous one will be calculated as well as the estimate of the population size and the signalling when the CV is greater than 20% and segmented by the demographic and territorial variables.

To analyse factors associated with variables of a given measurement or variables measuring the change between one measurement and another, we will use multivariate explanatory models adapted to the characteristics and nature of the variables and specified as generalized linear mixed models (GLMM) with a family dependent on the type of dependent variable: Gaussian, when the variable is continuous (equivalent to a linear regression); binomial, when the variable is dichotomous (equivalent to a logistic regression); or Poisson, when the variable is discrete (equivalent to a Poisson regression). Random effects will be included in these models with two goals: first, capture the effects of unobserved confounders, and second, capture the time dependency (as you will get repeated measures of the subjects), and the spatial dependency (i.e., spatial clustering), if applicable. Inferences will be made following a Bayesian perspective and using the integrated nested Laplace approximation (INLA) [82,83]. We will use penalised complexity priors known as PC priors. These priors are robust in the sense that they do not impact the results and, in addition, they allow for an epidemiological interpretation [84]. The analyses will be carried out using free software R (version 4.0.4 or greater) [81] through the INLA package [82,83,85].

Finally, advanced data visualisations will be used to allow an in-depth exploratory analysis of the evolution of the study variables and a representation of the main results of the produced models. These visualisations will be developed using Python [86] programming language and integrated into software and web solutions that allow for interaction and dissemination.

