Economic situation and socio-demographic characteristics	Educational level, employment situation, working from home, type of contract, occupation ^c^, cohabitation with a partner, identification of the cohabitant with the greater income (educational level, employment situation, type of contract, occupation), difficulty in making ends meet, late payments, income, future worries, and degree of confidence in public institutions.	Employment situation, educational level, occupation ^c^, development ^b^, ability to work, identification of the cohabitant with the greater income (educational level, employment situation, occupation), difficulty in making ends meet, late payments, change in economic situation, parents’ educational level, and future worries.	Employment situation, educational level, occupation ^c^, development, ability to work, identification of the cohabitant with the greater income (educational level, employment situation, occupation), difficulty in making ends meet, late payments ^b^, change in economic situation, parents’ educational level, and future worries.	Employment situation, educational level, occupation ^c^, development, ability to work, identification of the cohabitant with the greater income (educational level, employment situation, occupation), difficulty in making ends meet, late payments ^b^, change in economic situation, parents’ educational level, and future worries.

^a^ Questionnaires are provided in Supplementary Material 2. ^b^ Variables that present modifications in their temporal scope in relation to the previous measurement. ^c^ Composite variables: emotional well-being [75], social and emotional support [76,77], body mass index [78], social class [79,80].

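### The change tables in section 2.10 express change as percentages and population counts after dichotomising the shared variables; adding a full-scale change would recover information, mainly for small shifts and segments

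*Protocol article*

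**What the plan says.** Section 2.10 of the protocol article builds its tables in steps.

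1. Each variable is first described at each measurement on its own scale: "A table will be prepared for each variable of each measurement, together with the variable’s original response categories". The content includes "the relevant statistic (mean or percentage), the 95% CI, and the coefficient of variation (CV"), in total and by sex and age, province and urbanisation.
2. Then: "The variables shared by all measurements are dichotomized based on the results reported in the previous tables". The category shown is "the most convenient category to be highlighted based on the previous tables".
3. For change against M1, "both the population affected by the change and the percentage segmented per demographic and territorial variables will be estimated". A p value is attached to this step; it "will be indicated in a footnote to the table using three categories".
4. For consecutive pairs of measurements, "the estimated percentage of the difference between one measurement and the previous one will be calculated", with a population size and a flag for high CV. No p value is mentioned here.
5. Later in the section, factors associated with a variable or with a change are modelled by Bayesian mixed models with Gaussian, binomial or Poisson family. No ordinal family is named.

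The outcomes most affected are those of the first hypothesis in section 1.3: general health, mental health and emotional well-being. Table 5 lists all three from M1 onward. Its footnote reads "Composite variables: emotional well-being [75], social and emotional support [76,77], body mass index [78"], and adds social class. Social and emotional support, and weight and height, first appear at M2.

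**The concern.** This point is about the scale on which change is measured. It would hold even if every cut were fixed in advance; the choice of cut from the results is a separate matter.

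When a score or an ordered item is reduced to two groups, movement within either group does not enter the change estimate. The contrast and its p value then use less information than was collected. That matters most where the sample is thinnest, and section 2.10 segments change by demographic and territorial variables. A modest deterioration in well-being that mostly stays on one side of the cut could earn no p-value footnote in those tables, although the data already held would show it on the full scale.

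**Working it through.** **The plan's own figure.** Section 2.4 gives p = q = 0.5, precision 2.4 points, 95% confidence, design effect 1.8 and non-response 40%.

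- Effective n = 1.8 × 1.96² × 0.25 / 0.024² = 3001
- Theoretical n = 3001 / 0.60 = 5002

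The stated figures of about 3000 and 5000 reproduce. The survey is sized for the precision of a percentage. The article gives no target effect, SD, category distribution, cut point or power for any outcome, so everything below rests on assumptions, with two-sided 5% tests.

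**Normal score, independent samples.** Relative efficiency of a cut with tail share p against the full score is RE = φ(z_p)² / [p(1−p)]. If the full-scale test has 80% power, the dichotomised test has power Φ(2.80·√RE − 1.96).

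| Cut at | RE | Information lost | 80% falls to |
|---|---|---|---|
| 50% | 0.399²/0.25 = 0.637 | 36% | 61% |
| 30% | 0.348²/0.21 = 0.576 | 42% | 57% |
| 20% | 0.280²/0.16 = 0.490 | 51% | 50% |

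**Within-person change.** RE = {φ² / [p(1−p)]} × (1−ρ) / (1−r), where r is the correlation of the two binary indicators implied by a bivariate normal with correlation ρ.

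- Cut 50%, ρ = 0.4: r = 0.262, RE = 0.637 × 0.6/0.738 = 0.52
- Cut 50%, ρ = 0.6: r = 0.410, RE = 0.637 × 0.4/0.590 = 0.43
- Cut 20%, ρ = 0.7: r = 0.456, RE = 0.490 × 0.3/0.544 = 0.27

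Over cuts of 50–20% and ρ of 0.4–0.7, RE is 0.27–0.52, a loss of 48–73%.

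**Five-category item under proportional odds.** RE = 3c(1−c) / (1 − Σp_k³), with c the cumulative share at the cut. The best cut for three assumed distributions is:

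- (10, 45, 30, 10, 5)%, c = 0.55: 0.7425/0.8798 = 0.844; 80% falls to 73%
- (20, 50, 20, 7, 3)%, c = 0.70: 0.63/0.8586 = 0.734; 80% falls to 67%
- (10, 20, 40, 20, 10)%, c = 0.30: 0.63/0.918 = 0.686; 80% falls to 64%

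The loss is 16–31% at the best cut. Cuts that isolate a small category lose more: in the first example, c = 0.10 gives 0.27/0.8798 = 0.307.

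**Where the loss matters.** Take 3000/1.8 = 1667 effective people per measurement, treated as independent samples, and a normal score.

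- Total sample, shift 0.097 SD: 80% power on the score; 61, 57, 51 and 39% for cuts at 50, 30, 20 and 10%.
- Total sample, shift 0.2 SD: at least 94% power even with the 10% cut.
- One eighth of the sample (1667/8 = 208; two sexes by four age bands, taken as equal in size), shift 0.274 SD: 80% on the score; 60, 58, 53 and 41% for the same cuts.

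**The case against.** A reader might infer that the study evaluates change only through dichotomies. The article does not support that. Section 2.10 reports a mean or percentage with 95% CI at each measurement on the original categories, so a shift that misses the cut can still be seen by comparing tables. It also plans Gaussian mixed models for change variables, with random effects for repeated measures. The expectation in section 1.3 of greater impact in women, young people and those diagnosed with COVID-19 is a question about associated factors, which those models address. What they do not supply is the design-weighted estimate and test of how much the population changed, and they name no family for ordered outcomes.

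A reader might also quote a fixed loss of power as a property of this plan. There is none: no distribution or target effect is given, and the figure depends on which test is anchored. With the dichotomised test held at 80%, the gap cannot exceed 20 points; with the full scale held at 80%, a 70% information loss costs about 46 points.

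Three further objections stand in part.

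- The response formats and the well-being instrument are not shown, so it is an assumption that self-perceived health is an ordered item and that emotional well-being behaves like a roughly normal score. Composite does not imply scored; social class carries the same label.
- The dichotomising sentence covers variables shared by all measurements. The article does not say outright that consecutive differences use the same dichotomies, only that they are expressed as percentages and counts. Nor does it say that the footnoted p values are the test of the first hypothesis.
- Percentages and numbers of people affected are a legitimate target for a population health survey and match its sample-size basis. That is a reason to keep them, not a reason to leave out the full-scale change.

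**Conclusion.** The point holds for the change tables of section 2.10. They estimate change as percentages and population counts after dichotomising the shared variables, and they contain no mean or ordinal change. It applies to emotional well-being if it is scored, and to self-perceived general and mental health if they are ordered items.

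The size depends on assumed distributions, cuts and correlations: roughly a third to a half of the information for a normal score in independent samples, a sixth to just under a third for a five-category item at its best cut, and about half to three quarters for within-person change. The practical cost is in small shifts and in the segments. For a shift of 0.2 SD or more in the total sample it is slight. Social and emotional support and body mass index start at M2 and so have no change against M1; for them the point concerns the consecutive differences only. This is a worthwhile gain in precision and does not invalidate the planned tables.

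**What to change.** In the change tables of section 2.10:

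- For scored variables, add the design-weighted mean change with 95% CI and p value.
- For ordered items, add a design-based ordinal comparison (such as proportional odds) or a rank comparison, with 95% CI and p value.
- Use the same weights and variance estimation as for the percentages.
- Keep the dichotomised percentages and population counts in adjacent columns.
- For variables first collected at M2, apply this to the consecutive differences only.

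The cost is a few more columns and some analysis code; no new data are needed. An ordinal summary is harder for lay readers than a percentage, and proportional odds adds a modelling assumption; retaining the percentages limits the first drawback, and the rank comparison avoids the second.

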### 2.4. Sample Size

The ESSOC is made up of a series of measurements for each population study group (general, zones and +55) with a total of 22,000 effective interviews being carried out over three years. As of June 2021, almost 13,000 effective interviews have been conducted.

During the first measurement (M1), the ESSOCgeneral scope started with a random ‘teorical’ sample comprised of 5000 people. This sample includes respondents and non-respondents for whatever the reason for not responding. Its sample size was calculated under the assumptions of maximum variability in the estimate (p = q = 0.5), a precision of 2.4 percentage points for estimates in Andalusia, a confidence level of 95%, a non-response rate of 40% (whatever the reason) and a design effect of 1.8. The subsequent measurements (M2–M5) are comprised of the longitudinal theorical samples of the previous measurements and, in addition, of a new theorical sample in each measurement. That new theoretical sample is selected according to the design of the first measurement, except for M5 which will incorporate a new stratum of ‘residing or not in disadvantaged areas’ [60]. Finally, due to non-response, from these longitudinal and new theoretical samples an ‘effective sample’ is obtained for each measurement. Thus, those effective samples include just the respondents. With respect to the theoretical sample size for the longitudinal sample of a measurement, this is defined by the effective longitudinal sample and the effective new sample from the previous measurement. To maintain the effective sample size provided by the first measurement of the ESSOCgeneral, the aim for the subsequent ones is to reach an effective sample about 3000 people per measurement, while the effective sample size for ESSOCzones has been established at 2750 people and at least 1350 for ESSOC + 55, assuming theoretical response rates of 60% (considering all types of indidents).

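### A 20% CV signal on the net difference between consecutive measurements marks every change smaller than five standard errors, so precisely estimated stability is signalled in the same way as noise.

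*Protocol article*

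**What the plan says.** Section 2.10 (Data Analysis) sets three reporting rules that matter here.

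- **Levels.** Each variable at each measurement is tabulated with n, the estimate, a 95% CI and the CV. "In the case of cells with CV estimates >20%, the CV will be indicated in a footnote to the table".
- **Change from M1.** A separate paragraph is meant "to evaluate the changes in each measurement with respect to the first one". Here a p value is "indicated in a footnote to the table using three categories: *p* < 0.001, *p* < 0.05, and *p* < 0.1".
- **Change between consecutive measurements.** This rule covers M2–M1, M3–M2 and M4–M3, for the variables that both members of a pair share. The plan states that "the estimated percentage of the difference between one measurement and the previous one will be calculated". Results are broken down by demographic and territorial variables. A marking rule is added for the same tables: "as well as the estimate of the population size and the signalling when the CV is greater than 20" per cent. The paragraph names no SE, confidence interval or other precision criterion for these differences.

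Section 2.4 (Sample Size) supplies the precision inputs: "maximum variability in the estimate (p = q = 0.5), a precision of 2.4 percentage points for estimates in Andalusia". The same calculation also assumes "a confidence level of 95%, a non-response rate of 40% (whatever the reason) and a design effect of 1.8".

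**The concern.** The CV is the standard error divided by the estimate. It works as a precision mark for a level that lies well away from zero. A net difference has no such anchor: as the true change approaches zero the CV grows without limit, however small the standard error. The third rule therefore cannot tell a precise finding of no change from an imprecise estimate.

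This matters because following the evolution of health and its determinants is among the specific objectives (section 1.4), and the overlapping panel was chosen so that longitudinal as well as cross-sectional estimates are available (section 2.1). A reader who has met the 20% threshold in the level tables is likely to read it the same way in the change tables, where it means something else. Well-estimated stability, and moderate changes with strong statistical support, would carry the same mark as noisy cells.

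**Working it through.** **Inputs.** From section 2.4: p = q = 0.5, half-width 2.4 points, 95% confidence, design effect 1.8, non-response 40%, about 3000 effective interviews per measurement. From section 2.10: the 20% CV threshold and the p categories 0.001, 0.05 and 0.1 (sidedness not stated; two-sided assumed). The correlation r between consecutive estimates that panel overlap induces is not given; r = 0 to 0.7 is assumed.

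**1. The plan's own sample size.** n = 1.8 × 0.25 × (1.96/0.024)² = 3001 effective, and 3001/0.60 = 5002 theoretical. This reproduces the stated 3000 and 5000, so the inputs can be used for standard errors.

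**2. What the threshold means for a difference d.** CV(d) = SE(d)/|d| > 0.20 is equivalent to |d| < 5 SE(d). A change at the threshold has |z| = 5, two-sided p = 5.7 × 10⁻⁷. For comparison:

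| p | \|z\| | CV |
|---|---|---|
| 0.1 | 1.64 | 60.8% |
| 0.05 | 1.96 | 51.0% |
| 0.001 | 3.29 | 30.4% |
| 5.7 × 10⁻⁷ | 5.00 | 20.0% |

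This step is algebra and does not depend on sample size, design effect or r.

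**3. Size in percentage points, whole sample, p = 0.5.** One level: SE = √(1.8 × 0.25/3000) = 1.22 points, CV = 1.22/50 = 2.4%, far from the signal. For the difference, SE(d) = 1.225 × √(2(1 − r)):

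| r | SE(d) | p<0.05 from | p<0.001 from | signalled below |
|---|---|---|---|---|
| 0 | 1.73 | 3.4 | 5.7 | 8.7 |
| 0.5 | 1.22 | 2.4 | 4.0 | 6.1 |
| 0.7 | 0.95 | 1.9 | 3.1 | 4.7 |

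The thresholds shrink at lower prevalence. At p = 0.2 and r = 0, p<0.001 starts at 4.6 points and the signal stops at 6.9.

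**4. Probability of being signalled**, Φ(5 − t) − Φ(−5 − t), for a true change of t standard errors: above 0.999999 at t = 0; 0.96 at t = 3.29; 0.84 at t = 4; 0.50 at t = 5. A true null whose 95% CI is only ±3.4 points (r = 0) or ±1.9 points (r = 0.7) is thus almost certain to be signalled.

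**5. A territorial segment.** Assume 375 people (3000/8; actual provincial sizes differ because allocation is proportional to population). The level CV is √(1.8 × 0.25/375)/0.5 = 6.9%, unsignalled. The difference has SE 4.90 points at r = 0, so the signal stops only at 5 × 4.90 = 24.5 points. At r = 0.7 it stops at 24.5 × √0.3 = 13.4 points.

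**6. Overlap with the p-value rule.** P values are planned for changes from M1, CV signals for consecutive pairs. The one contrast under both rules is M2–M1. There, a change with 3.29 < |z| < 5 would be both p<0.001 and signalled.

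**The case against.** **The wording may mean something else.** The sentence does not say which estimate the CV belongs to. The paragraph before it pairs a percentage with the number of people affected by the change, and the consecutive-pair sentence has a similar pairing. If the quantity is the share of people who changed, it is a positive proportion and a CV mark is ordinary practice: for 10% changers at n = 3000 and design effect 1.8, CV = √(1.8 × 0.1 × 0.9/3000)/0.1 = 7.3%. This reading cannot be excluded. A difference between one measurement and the previous one is nevertheless most naturally a net difference. Attaching the CV to the population size does not help either: if that size is N × d with N treated as known, its CV equals that of d.

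**It is only a table convention.** True. The signal changes no estimate, and section 2.10 analyses the factors associated with change by GLMM, which does not use it. That limits the consequence but does not make the mark informative.

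**An absolute precision rule has its own faults.** Also true. A fixed half-width in points ignores prevalence and would seldom mark an outcome of about 2%, even where the estimated change is smaller than its own error. No such cut-off is proposed here.

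**Conclusion.** The point holds for net differences. The 20% CV signal on consecutive-measurement changes is a five-standard-error rule. It marks any stable indicator regardless of precision, and with the plan's inputs it marks overall changes up to about 8.7 points (independent measurements) or 4.7 points (assumed r = 0.7). The equivalence is exact. The point figures rest on p = 0.5, n about 3000, design effect 1.8 and the assumed correlations. What is at stake is the interpretation of the descriptive change tables.

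A reader might infer more than the document supports:

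- That signalled cells are declared unreliable. The text speaks only of signalling and states no suppression or quality label.
- That nearly all change cells will be marked. This depends on the sizes of the true changes, which are unknown.
- That every change with p<0.001 is marked, or that the two marks clash throughout. Changes beyond 5 SE escape, and only M2–M1 falls under both rules. Even there, the text does not say that both marks share a table.
- That the level-table footnote has the same fault. It does not, since the CV is a suitable mark for levels.

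**What to change.** State in section 2.10 which quantity the consecutive-pair tables report. If it is the share of people who changed, say so and keep the CV rule.

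If it is the net difference:

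- keep the CV signal for level estimates and their population totals;
- for each net difference, replace the signal with the difference and its SE or 95% CI;
- if a quality mark is still wanted, base it on the CVs of the two component levels or on the cell's sample size, not on the CV of the difference.

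The cost is a reworded sentence, one more column in the change tables and a small change in the table code. No new data are needed and no estimate changes.

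### The model rules in section 2.10 give every discrete outcome a Poisson likelihood, credit random effects with capturing unobserved confounders, and say the priors do not affect results; none is right as written

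*Protocol article*

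**What the plan says.** Section 2.10 (Data Analysis) of the protocol article sets out generalized linear mixed models for factors associated with "variables of a given measurement or variables measuring the change between one measurement and another". The family follows from the type of outcome: Gaussian for a continuous variable; "binomial, when the variable is dichotomous (equivalent to a logistic regression"); and "Poisson, when the variable is discrete (equivalent to a Poisson regression"). No other family is named, and the rule draws no line between levels and changes.

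The section then gives the purpose of the random effects: "Random effects will be included in these models with two goals: first, capture the effects of unobserved confounders". A second, separate goal is to "capture the time dependency (as you will get repeated measures of the subjects), and the spatial dependency (i.e., spatial clustering), if applicable".

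Inference is Bayesian by INLA with penalised complexity (PC) priors, of which the article says: "These priors are robust in the sense that they do not impact the results".

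Earlier in the same section, variables common to all measurements are dichotomised. That text describes tables; it does not say that the models use the dichotomised form.

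**The concern.** These are positive statements about method, so they cannot be set aside as detail that a condensed article leaves to a fuller plan.

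- **Likelihood.** Table 5 lists items such as self-perceived general and mental health, happiness and difficulty in making ends meet. The article gives no response scales. If such items are ordered and are modelled without dichotomising, the only branch of the rule that fits them is Poisson. A signed change in a discrete item takes negative values, to which Poisson gives zero probability.
- **Confounding.** A confounder is by definition associated with the exposure. A standard random effect is assumed independent of the covariates. It describes heterogeneity and dependence; it does not adjust for an unmeasured common cause.
- **Priors.** PC priors shrink towards the simpler model. They act on the posterior by design, most visibly for a variance estimated from few groups.

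These models serve the determinants and inequality objectives in section 1.4. What is at stake is the precision reported for ordered outcomes, and whether readers take the associations as adjusted for unmeasured confounding.

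**Working it through.** The article gives no figure on this point and no outcome distribution, so every distribution and correlation below is an assumption.

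**1. Poisson on an ordered item.** Assume five levels with shares 15, 35, 30, 15 and 5%. Coded 1-5, the mean is 0.15 + 0.70 + 0.90 + 0.60 + 0.25 = 2.60 and the variance is 7.90 − 2.60² = 1.14. Coded 0-4, the mean is 1.60 and the variance is unchanged.

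Ratio of Poisson to true standard error = √(mean/variance). Power of a test designed for 80% = Φ(2.80 − 1.96 × ratio).

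| Coding | Ratio | Power |
|---|---|---|
| 1-5 | √(2.60/1.14) = 1.51 | Φ(2.80 − 2.96) = 44% |
| 0-4 | √(1.60/1.14) = 1.18 | Φ(2.80 − 2.32) = 68% |

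(Rounding the second ratio to 1.18 before use gives 69%.) Two other assumed items coded 1-5, with mean 3.25 and variance 0.99 and with mean 3.87 and variance 0.79, give ratios of 1.81 and 2.21. In simulation with 3000 people, nominal 95% intervals covered 99.9% and 100%. Adding random effects does not help, because they can only raise a Poisson variance.

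The error reverses for overdispersed counts. With mean 3, variance-to-mean ratios of 2.5 and 4 and no extra-variation term, standard errors are 0.63 and 0.50 of the true value, and coverage is 78% and 67%. An observation-level random effect could absorb that.

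**2. Signed changes.** Take an item with mean 3.25 at two measurements and assume that 70%, 50% or 30% of people keep their answer, the rest answering afresh. The share of negative changes is then 11%, 18% or 25%. All of these lie outside Poisson support.

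**3. Random intercepts and an unobserved confounder.** The true effect is set to 0. Assume outcome SD 1, half the outcome variance due to the confounder, a correlation of 0.4 between the confounder and the stable part of the exposure, exposure intraclass correlation 0.5 to 0.7, and 2000 people.

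| Measurements | Random-intercept estimate (SD) | Within-person estimate |
|---|---|---|
| 2 | 0.14 to 0.19 | 0.00 |
| 5 | 0.07 to 0.11 | 0.00 |

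Under a stronger setting (exposure-confounder correlation about 0.7, four measurements, confounder coefficient and residual SD both 1), a time-varying exposure gives 0.40 against 0.69 by ordinary least squares, and 0.00 once the person mean is added. A time-constant exposure gives 0.71, identical to ordinary least squares. The random intercept therefore removes part of the bias for time-varying exposures and none for fixed ones.

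**4. PC prior.** Assume 8 groups (the number of provinces in section 2.5) of 375 people, residual SD 1, true between-group SD 0.10, and a prior with tail probability 0.01 above a scale U. Moving U from 0.1 to 3 moves the average posterior mean of the between-group SD from about 0.07 to about 0.11.

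**The case against.** The best defence is that the wording is loose but the intent is sound. Set beside continuous and dichotomous, the word discrete may be shorthand for counts, and the paragraph opens by saying that models will suit the nature of each variable. Variables shared by all measurements are dichotomised, and self-perceived health is one of them; modelled in that form it is binomial. Change is reported earlier in section 2.10 as the population and percentage affected, which suggests a change status rather than a signed score.

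Much of this stands. A reader might infer that self-rated health will be fitted as Poisson; the article does not say so. It does not say the opposite either. The dichotomising is described for tables and does not reach items absent from the first measurement, such as happiness, which Table 5 lists only from the second.

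A reader might also infer that signed changes would yield wrong intervals unnoticed. They would not: the fit would fail, and the analyst would see it. Nor is 1.5 a lower bound on the inflation, since recoding the same item from 0 gives 1.2.

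On confounding, a reader might infer that the random effects create it. They do not; residual confounding is present in any observational regression. The fault is the claim that they capture it. A within-person contrast also cannot rescue the inequality axes in section 1.4, which are largely fixed within a person.

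On priors, the article never names province as a random effect, and finer geography is available (section 2.9, Table 4). The eight-group case is an illustration only.

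**Conclusion.** The point holds for the three statements as worded. The confounding and prior claims are wrong in general. The Poisson rule is wrong for ordered items modelled undichotomised and unusable for signed discrete changes; it does no harm to items modelled as dichotomous, and true counts belong under it.

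For the assumed ordered item with variance 1.14, standard errors are 1.2 to 1.5 times too large depending on coding, and 80% power becomes about 68% or 44%. Under the weaker confounding setting, a null effect appears as 0.07 to 0.19 SD for a time-varying exposure; for a fixed exposure nothing is removed. These sizes rest on assumed distributions and correlations, and other inputs would change them.

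The documents do not support saying that the study's published intervals or associations will be wrong: they do not show which items will be modelled in which form. What they support is that the stated rules permit these errors and would lead readers to overrate the adjustment. This should be corrected, and correcting it is cheap.

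**What to change.** In section 2.10:

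1. Restrict Poisson to counts, with negative binomial as the alternative when they are overdispersed. Name a cumulative-logit likelihood for ordered items, and an ordinal or Gaussian model for signed changes.
2. Replace the reference to unobserved confounders by unobserved heterogeneity, and do not describe associations as adjusted for unmeasured confounding. For time-constant factors such as gender and ethnicity, this wording change is the whole remedy.
3. For each time-varying covariate, enter the person mean and the deviation from it, and report the within-person coefficient.
4. Delete the statement that the priors have no impact, and report one fit under a different prior scale.

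The cost is a revised paragraph and a few extra model fits in R, with no new data. Within-person coefficients are less precise, and are unavailable for factors that do not vary over time. By section 2.2, the fifth general-population measurement, both disadvantaged-area measurements and the second over-55 measurement were still to come, so the wording can be settled before those are analysed.
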